## Abstract

The early unfractionated heparin (UFH) treatment in patients with ST-elevation myocardial infarction (STEMI) is a single-center, open-label, randomized controlled trial. The study population are patients with STEMI that undergo primary percutaneous coronary intervention (PPCI). The trial was designed to investigate whether early administration of unfractionated heparin immediately after diagnosis of STEMI is beneficial in terms of patency of infarct-related coronary artery (IRA) when compared to established UFH administration at the time of coronary intervention. The patients will be randomized in 1:1 fashion in one of the two groups. The primary efficacy endpoint of the study is Thrombolysis in myocardial infarction (TIMI) flow grades 2 and 3 on diagnostic coronary angiography. Secondary outcome measures are: TIMI flow after PPCI, progression to cardiogenic shock, 30-day mortality, ST-segment resolution, highest Troponin I and Troponin I values at 24 hours. The safety outcome is bleeding complications. The study of early heparin administration in patients with STEMI will address whether pretreatment with UFH can increase the rate of spontaneous reperfusion of infarct-related coronary artery.

## Introduction

Ischemic heart disease is the leading cause of death worldwide, accounting for 20% of all deaths in Europe. STEMI accounts for considerable part of cardiovascular disease morbidity and mortality with incidence in Europe ranging from 43–144/100,000 per year and from 50/100,000 per year in the US. Mortality at 1 year in STEMI patients treated with coronary angiography is reported at approximately 10%. Immediate PPCI and opening of occluded coronary artery is the most important intervention that reduces STEMI-related mortality and morbidity [1].

Guidelines for the management of patients with STEMI only recommend unfractionated heparin (UFH) at the time of PPCI, and the data on early treatment with UFH at the time of diagnosis are scarce [1, 2]. Contrary to the international guidelines, our center has been using UFH at the dose of 70–100 IE/kg as a pretreatment immediately once the diagnosis of STEMI and the decision for PPCI was made.

In Slovenia, a country with around 2,000,000 inhabitants, STEMI patients are referred to one of two 24/7 catheterization laboratories. University Medical Centre of Ljubljana is one of them and covers around 1,200,000 inhabitants. If a doctor in the emergency room suspects myocardial infarction consultation with an intensive care physician/cardiologist is made. Based on the electrocardiogram and the clinical picture, the cardiologist decides whether to refer the patient directly to a cath lab or to the nearest emergency room. The consulting doctor will also advise on the medication to be used. Patients referred directly to the cath lab will be given aspirin 250/500 mg po and approximately 100 units/kg UFH. Pre-treatment with P2Y12 is not administered.

In the recent COOL AMI EU Pivotal trial and the COOL AMI EU Pilot, the multicenter, prospective randomized controlled trials, we noticed a higher proportion of spontaneous reperfusions of culprit artery in our patients, receiving early UFH in the field when compared to other centers without early UFH treatment [3, 4].

In the proposed trial, we intend to investigate effectiveness and safety of early UFH administration compared to late administration at the time of coronary intervention.

## Materials and methods

### Participants, interventions and outcomes

#### Study objectives

Early unfractionated heparin treatment in patients with STEMI is a single-center, open-label, randomized controlled trial and will determine if early administration of UFH in the field at the time of established diagnosis and decision for PPCI is superior to the recommended application at the time of PPCI.

The trial is registered under www.clinicaltials.gov: NCT05247424.

#### Patient population

Study population will consist of 600 STEMI patients referred for PPCI at University Medical Centre of Ljubljana, Slovenia. Flowchart of the study is presented in Fig 1. Case report form is included as S1 Checklist.

**Fig 1 pone.0303376.g001:**
[figure not shown]
An overview of the timepoints for assessment of study endpoints.

*Inclusion criteria*. Inclusion criteria are based on standard definition of STEMI (at least two contiguous leads with ST-segment elevation ≥ 2.5 mm in men < 40  years, ≥2 mm in men ≥ 40  years, or  ≥ 1.5  mm in women in leads V_2_–V_3_ and/or ≥ 1 mm in the other leads in the absence of left ventricular hypertrophy or left bundle branch block) [1], with additional limitation for duration of symptoms.

Inclusion criteria are:

Adult patients with ST-elevation acute myocardial infarctionChest pain for less than 6 hours

*Exclusion criteria*. Exclusion criteria are:

Cardiac arrest without regaining consciousnessChest pain for more than 6 hoursHemodynamic impairment (cardiogenic shock)Pregnant women

### Assignment of interventions

Patient randomization is performed directly after establishing diagnosis of STEMI and decision for PPCI has been made. Randomization is in a 1:1 ratio to:

Immediate application of UFH intravenously at a dose of 70–100 units/kg on top of standard treatment. Additional UFH is added after diagnostic coronary angiography according to activated clotting time (ACT) when PPCI is performed.Standard treatment and application of intravenous UFH only after diagnostic coronary angiography at a recommended dose of 70–100 units/kg when PPCI is performed.

When the ER doctor calls the intensivist about an eligible STEMI patient, randomization is performed using random permutated blocks via secure online randomization service (www.sealedenvelope.com). The website can be opened on a smartphone or a computer. After entering the password for the study, the randomizing physician’s email is entered, followed by the unique patient ID. The inclusion and exclusion criteria are then checked and the “Randomize" field is clicked. The result of the randomization to group A–heparin on the field ‐ or B–no heparin ‐ is displayed on the screen and sent to the randomizing physician’s email. The doctor performing the randomization then informs the ER doctor about the therapy and dosage. We started randomizing patients on March 10^th^ 2022. Predicted end of the study is 31^st^ March 2025.

Upon arrival to the cath lab, immediate coronary angiography is performed via radial or femoral approach at the discretion of the interventional radiologist. ACT is measured in all patients who receive pretreatment with UFH and when PPCI is needed, an additional bolus of UFH is given for a target ACT of 250–350 seconds. In patients without pretreatment, UFH is administered according to guidelines [1] in the dose of 70–100 units/kg when PPCI is needed. Additional anticoagulation or glycoprotein IIb/IIIa (eptifibatide) can be administered at the discretion of the interventional cardiologist or an additional bolus of UFH is added in long procedures.

The vascular access site is closed with a closure device or manual compression. The patient receives a P2Y12 inhibitor at the discretion of the interventional cardiologist immediately after PPCI while still in the cath lab.

Patients are admitted to cardiac intensive care unit usually for a period of 24 hours; there, serial troponin I measurements are performed. Possible bleeding complications are prospectively monitored and recorded.

### Outcome definitions

#### Primary outcome

The primary efficacy endpoint of the study is TIMI [5] flow grade 2 or 3 on diagnostic coronary angiography.

#### Secondary outcomes

The secondary endpoints aim to assess infarct size, effectiveness of reperfusion, hemodynamic deterioration and survival [6–8]. Cardiogenic shock will be defined clinically (systolic blood pressure of less than 90 mmHg for longer than 30 minutes or the use of catecholamine therapy to maintain systolic pressure of at least 90 mmHg [8].

Secondary endpoints are:

Final TIMI flow grades 2 and 3Highest Troponin I valueTroponin I value 24 hours after PPCIST-segment resolution in a single lead with maximum baseline ST-segment elevationProgression to cardiogenic shock30-day mortality

### Safety endpoint

Safety endpoint will be the occurrence of bleeding according to the Bleeding Academic Research Consortium (BARC) definition 3–5 [9]. We do not expect serious bleeding complications in STEMI patients. A potential harm of heparin in the prehospital setting would be the case of misdiagnosis of STEMI, e.g. intracerebral hemorrhage with ECG changes or aortic dissection mimicking STEMI by impairing coronary flow. These complications are also closely monitored.

### Data collection, management, and analysis

#### Sample size calculation

Several published observational studies have investigated pretreatment with UFH [10–13]. The reported difference in rates of spontaneous reperfusion varies and depends on the time between UFH administration and PPCI.

In a propensity-matched study of 552 matched patients, Bloom et al. reported a significantly lower proportion of patients with a TIMI 0 or 1 flow in the IRA in those who received UFH in fixed bolus doses of 4000 units and 1000 units at hourly intervals during transport prehospital (66% vs. 76%, p<0.001) compared with those who did not [11]. Investigators in the observational substudy of the TASTE trial reported a lower incidence of TIMI 0 or 1 in patients who received an average of 5000 units of UFH pre-hospital or in the emergency department (73.1% vs. 80.9%, p<0.001) compared to those who did not [12]. Another observational study by Giralt et al. also showed that pretreatment with UFH in a fixed intravenous dose resulted in a lower rate of TIMI 0 or 1 (69.7% vs. 78.8%, p<0.001) compared to the post-treatment group. In addition, the time-dependent effect of UFH administration was evident with higher rates of spontaneous reperfusion (TIMI 2 or 3) with shorter duration of administration from symptom onset [13].

The sample size calculation for this study is based on the historical baseline rate of TIMI 0 or 1 in STEMI patients arriving at our clinical center and the estimated benefit of prehospital UFH administration from the previously mentioned studies. The historical baseline rate of TIMI 0 or 1 flow at the University Medical Centre of Ljubljana is 58.5% with UFH pretreatment. We designed the study to detect a difference of 11.5% in the experimental group, which corresponds to 70% of patients with TIMI 0 or 1. To achieve a power of 80% for detecting this difference at a significance level of 5%, a total of 538 patients are required. In addition, we considered a dropout rate of 2.5%, which increases the total sample size required to 598. Sample size was calculated using the Sealed Envelope Ltd. 2012 Power Calculator for Binary Outcome Superiority Trial Web Application (https://www.sealedenvelope.com/power/binary-superiority/).

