#### Data analysis

All data will be analyzed according to the intention-to-treat principle. Fisher’s exact test will be used to compare TIMI 2 or 3 flow rates in both arms. An odds ratio with a 95% confidence interval will be calculated as an estimator of early UFH administration.

For all secondary endpoints, the effect of early UFH administration with a corresponding 95% confidence interval will be estimated.

We assume there will be very little missing data for primary endpoint analysis. Missing data for secondary endpoints will be replaced by imputation of missing data.

Pre-defined subgroup analysis will be performed for sex, age (<65 years vs. >65 years), culprit artery (left anterior descending, left circumflex, right and side branch), time from onset of symptoms to heparin administration (<2 hours, 2–4 hours, >4 hours), and time from heparin administration to diagnostic angiography (<1 hour, >1 hour).

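### A 2.5% dropout rate takes 538 patients to 552, not to the stated 598; the allowance behind 598 needs to be stated.

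*Protocol article*

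**What the plan says.** The protocol article, under Sample size calculation, takes a TIMI 0 or 1 rate with pretreatment from the centre's own history ("The historical baseline rate of TIMI 0 or 1 flow at the University Medical Centre of Ljubljana is 58.5% with UFH pretreatment") and sets the comparison rate 11.5 percentage points higher ("which corresponds to 70% of patients with TIMI 0 or 1"). For 80% power at the 5% level it concludes that "a total of 538 patients are required". It then adds the allowance: "In addition, we considered a dropout rate of 2.5%, which increases the total sample size required to 598". Under Patient population the total is rounded up: "Study population will consist of 600 STEMI patients referred for PPCI". The article states no other inflation factor and no crossover or non-adherence rate.

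**The concern.** The base figure, the dropout rate and the final figure are all printed in the same paragraph, and the last does not follow from the other two. The gap is too large to be rounding, and the enrolment target of 600 rests on it.

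As the sentence stands, a reader cannot tell whether the trial planned to lose about 15 of 598 patients (2.5%) or about 60 (10%), or whether the allowance was for something other than loss. Actual attrition therefore has no clear planning figure to be judged against, and the power at the target is undetermined.

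**Working it through.** **Inputs** (Sample size calculation unless noted): TIMI 0 or 1 rates of 58.5% and 70%; power 80%; significance level 5%; 538 before the allowance; 2.5% dropout; 598 after it. Allocation is 1:1 (Assignment of interventions). The primary test is Fisher's exact test (Data analysis). The article does not say whether the 5% is one- or two-sided. Two-sided is assumed here because it reproduces 538.

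**Step 1: the base figure.** Unpooled normal formula for two proportions:

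n per arm = (1.960 + 0.842)² × [0.585 × 0.415 + 0.70 × 0.30] / 0.115² = 268.7, so 269 per arm and 538 in total. This matches the plan. Other variants do not: pooled variance gives 544, continuity correction 578, and a one-sided test (pooled) 428.

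**Step 2: the stated allowance.**
- 538 / (1 − 0.025) = 551.8, so 552.
- 538 × 1.025 = 551.5, so also 552.
- Stated: 598. The difference is 598 − 552 = 46 patients, or 46/552 = 8.3%.

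**Step 3: what does give 598.**
- *10% loss:* 538 / 0.90 = 597.8, so 598. Working backwards, 1 − 538/598 = 10.0%.
- *2.5% crossover in each arm* (an assumption; the article does not state it): the rates dilute to 0.975 × 58.5% + 0.025 × 70% = 58.79% and 0.975 × 70% + 0.025 × 58.5% = 69.71%, a difference of 10.925 points. The formula of step 1 gives 298.2, so 299 per arm and 598 in total. The common shortcut 269/0.95² = 298.06 also gives 299 per arm, although starting from the unrounded 268.7 it gives 596 in total.

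**Step 4: power at 598 under each reading.**

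| Meaning of the allowance | Evaluable | Power, plan's formula | Power, Fisher's exact test |
|---|---|---|---|
| 2.5% simple loss | 598 × 0.975 = 583 | 83% | 80.6% (at 291 per arm) |
| 10% simple loss | 598 × 0.90 = 538 | 80.0% | 77.3% (at 269 per arm) |
| 2.5% crossover per arm, no loss | 598 | 80.1% | 77.3% (at 299 per arm) |

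The Fisher figures come from exact enumeration at the stated or diluted rates. The gap between the two power columns arises because the sample size formula is not that of the planned test. The dropout step did not cause it, but it bears on how the sentence is corrected.

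**The case against.** The strongest reply is that 598 may be right and only one word wrong. The crossover reading keeps both printed numbers, 2.5% and 598, whereas the 10% reading has to discard the 2.5%. On that reading the trial has its designed 80% power by the plan's formula and nothing needs recalculating. This stands as a possible origin. It does not make the text correct: the article speaks of dropout, mentions no crossover, and on this reading would contain no allowance for lost patients.

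Three stronger readings are tempting, and the article does not support them.

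- *The trial is underpowered because of this error.* By the plan's own formula, power at 598 is 80% or more on all three readings.
- *The 2.5% must be right, because 10% would contradict the Data analysis section.* That section says: "We assume there will be very little missing data for primary endpoint analysis". The statement concerns missing endpoint values. Under Research ethics approval, consent is obtained after randomisation, at the time of PPCI or later in the hospital stay. Patients could therefore be lost even though their angiogram was read. A 10% allowance is not shown to conflict with the statement, and the quick reading of the endpoint does not settle the matter.
- *The trial enrols 46 patients too many.* This follows only if simple 2.5% loss was intended, which cannot be established from the article.

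**Conclusion.** The sentence is wrong as written: no standard dropout adjustment takes 538 to 598 at 2.5%. The discrepancy is 46 patients (8.3% of 552) if simple loss of 2.5% was meant, or a factor of four in the stated loss rate if 10% was meant. If crossover was meant, the allowance is mislabelled. The article does not allow a choice between these, and none is preferred here.

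Severity is moderate. The target of 600 covers 598 on every reading, and no endpoint, test or allocation changes. What is undetermined is the planned loss and the power: 80.0% to 83% by the plan's formula, and 77.3% to 80.6% by Fisher's exact test. So the answer decides whether the planned test falls just above or somewhat below 80%. The conclusion rests on the plan's own rates, a two-sided 5% level and, for the third reading, equal crossover of 2.5% in both directions.

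**What to change.** Keep the enrolment target of 598/600. The sponsor should state which allowance produced 598 and reword the sentence to match:

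- *If 2.5% simple loss:* give the requirement as 552. Say that enrolling 598 leaves about 583 evaluable patients, with 83% power by the formula used and 80.6% by Fisher's exact test.
- *If 10% loss:* replace 2.5% with 10%. Say that 538 are expected to be evaluable, with 80.0% power by the formula and 77.3% by Fisher's exact test.
- *If 2.5% crossover per arm:* replace the word dropout. State 80.1% power by the formula at 598 (77.3% by Fisher's exact test), and say that no allowance for loss is included.

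If the allowance was none of these, the sponsor should state it with the matching total and power. Enrolment should not be cut to 552 to make the numbers agree: with 2.5% loss that leaves 538 evaluable and 77.3% power with the planned test. The cost is one corrected sentence, with no change to enrolment or conduct.

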#### Data analysis

All data will be analyzed according to the intention-to-treat principle. Fisher’s exact test will be used to compare TIMI 2 or 3 flow rates in both arms. An odds ratio with a 95% confidence interval will be calculated as an estimator of early UFH administration.

For all secondary endpoints, the effect of early UFH administration with a corresponding 95% confidence interval will be estimated.

We assume there will be very little missing data for primary endpoint analysis. Missing data for secondary endpoints will be replaced by imputation of missing data.

Pre-defined subgroup analysis will be performed for sex, age (<65 years vs. >65 years), culprit artery (left anterior descending, left circumflex, right and side branch), time from onset of symptoms to heparin administration (<2 hours, 2–4 hours, >4 hours), and time from heparin administration to diagnostic angiography (<1 hour, >1 hour).

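### The 80% power quoted at 538 patients does not belong to Fisher's exact test, which has about 77% there and needs about 576 evaluable; planned enrolment of 598–600 covers the gap only while losses stay below about 4%

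*Protocol article*

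**What the plan says.** The Sample size calculation section of the protocol article states: "To achieve a power of 80% for detecting this difference at a significance level of 5%, a total of 538 patients are required". The planning rates of TIMI 0 or 1 flow are a historical rate that "is 58.5% with UFH pretreatment" and "a difference of 11.5% in the experimental group, which corresponds to 70% of patients with TIMI 0 or 1". The total is then raised to 598 for a 2.5% dropout, using an online calculator for a binary superiority outcome. The Patient population section sets enrolment at 600.

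The Data analysis section says that Fisher's "exact test will be used to compare TIMI 2 or 3 flow rates in both arms", by intention to treat, and that "An odds ratio with a 95% confidence interval will be calculated". It expects very little missing data for the primary endpoint. Neither section mentions an allowance for the conservatism of the exact test.

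**The concern.** A power statement holds only for the test that will be run. Because the data are discrete, Fisher's test at a nominal two-sided 5% rejects less often than 5% of the time under the null, and so it has less power than the large-sample test at the same number of patients. If the 538 came from a large-sample formula, the 80% describes a test that the trial does not plan to use.

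This matters for what happens between 538 and 598. If 538 is the number that must be analysed, and the inflation is there only to protect it, then the protected number is too small for the named test.

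**Working it through.** **Inputs.** TIMI 0/1 rates of 70% and 58.5%, 80% power and a 5% level come from Sample size calculation; 1:1 allocation comes from Assignment of interventions. Sidedness is not stated. Two-sided is inferred because it reproduces 538, whereas the one-sided pooled formula gives 214 per arm (428). Which arm carries the 70% does not affect a two-sided calculation, and neither does working with TIMI 2/3 rates (30% and 41.5%) instead.

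**Step 1: reproduce 538.** Unpooled normal approximation, per arm:

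n = (z₀.₉₇₅ + z₀.₈₀)² × [p₁(1−p₁) + p₂(1−p₂)] / (p₁−p₂)²

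= (1.960 + 0.842)² × [0.70×0.30 + 0.585×0.415] / 0.115²

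= 7.849 × 0.452775 / 0.013225 = 268.7, rounded up to 269, total **538**.

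This matches exactly. The pooled formula gives 272 per arm (544). The continuity-corrected formula, which approximates the requirement of Fisher's test, gives 289 per arm (578). So 538 was not sized for Fisher's test.

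**Step 2: exact power of the named test.** All pairs of binomial outcomes were enumerated at the planning rates, summing the probability of those with two-sided p ≤ 0.05. The two usual definitions of the two-sided Fisher p-value gave the same power.

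| Analysed (per arm) | Fisher's exact | Uncorrected Pearson chi-square |
|---|---|---|
| 538 (269) | 77.3% | 79.9% |
| 552 (276) | 78.2% | 80.7% |
| 574 (287) | 79.9% | 82.3% |
| 576 (288) | 80.1% | 82.5% |
| 584 (292) | 80.8% | 83.0% |
| 598 (299) | 81.5% | 83.8% |
| 600 (300) | 81.7% | 83.8% |

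Among the sizes checked, Fisher's test first passes 80% at 576.

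**Step 3: why it loses power.** At 269 per arm and common event rates of 30% and 36%, the true size of Fisher's test is 4.05% and 4.12%. For the uncorrected chi-square it is 5.02% and 5.07%.

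**Step 4: what the planned enrolment delivers.**

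- At the stated 2.5% loss: 598 × 0.975 = 583 and 600 × 0.975 = 585, so about 584 analysed and Fisher power of about 80.8%.
- Loss at which Fisher's test drops to 80%: 1 − 576/600 = 4.0%, or 1 − 576/598 = 3.7%.
- Loss at which 538 remain from 598: 1 − 538/598 = 10.0%, with Fisher power of 77.3%.

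**Step 5: the dropout arithmetic.** 538/0.975 = 551.8, so 552. The 598 is 538/0.90 = 597.8, a 10% loss. The two ways of making the paragraph consistent are:

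- Dropout is 2.5% and the total is 552. Fisher power is 78.2% with everyone analysed and 77.3% once 538 remain.
- Dropout is 10% and the total is 598. About 538 are analysed, with power of 77.3%.

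Under either one, the named test misses 80%. It clears 80% only with the larger total and the smaller loss rate together, which is how the article now reads.

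**The case against.** The strongest reply is that nobody plans to analyse 538 patients. Enrolment is 598–600, the analysis is by intention to treat, little missing primary data is expected, and at the article's own dropout rate Fisher's test has just over 80%. This stands. A reader might infer that the planned analysis has only 77% power; the document does not support that, because 77% requires about four times the stated loss.

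It is also fair to say that Fisher's test is a legitimate choice. It guarantees a size at or below 5%, which the chi-square does not, and an unadjusted comparison in a randomised trial is valid. The power given up buys that guarantee.

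Two further criticisms are tempting and should not be pressed. One is that the odds-ratio interval will conflict with the Fisher p-value. The article names no interval method, and an exact interval would fit its wording. The other is that the effect will be reported only as an odds ratio. The text says that one will be calculated and does not exclude a risk difference, which an analysis plan could add.

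What the reply does not remove is the mismatch itself. The article fixes both the power statement and the test, so this is not a detail left to a later document. The margin that rescues the power comes from a dropout figure that does not agree with the total beside it.

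**Conclusion.** The statement that 538 patients give 80% power is wrong for the test named: the figure is about 77.3%, a shortfall of 2.7 points, and about 576 evaluable patients are needed. At planned enrolment with 2.5% dropout, power is about 80.8%, so the practical effect is small. It becomes real if losses pass about 4%, or if the dropout inconsistency is resolved by cutting the total to 552. The article describes deferred consent, which is one possible route to loss after randomisation, but it gives no rate for this.

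The result rests on a two-sided 5% level, equal arms and the article's own planning rates.

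**What to change.** Keep enrolment at 598–600. Restate the power for Fisher's test: 576 evaluable patients for 80%, or equivalently 77% at 538 and about 81% at 584. Reconcile the dropout figure by saying whether 2.5% or about 10% loss was meant. This changes only wording.

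Alternatively, change the primary analysis before database lock, and, because the trial is open-label, without sight of outcomes by arm. There are two options:

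- The uncorrected Pearson chi-square test with a matching confidence interval for the risk difference. Power is about 83.0% at 584 and 79.9% at 538, in line with how the trial was sized.
- A logistic model adjusted for age, sex and time from symptom onset to randomisation, reporting a standardised risk difference alongside the odds ratio. Age, sex and onset timing are already needed for eligibility or the planned subgroups. At the planning rates the odds ratio is (0.415/0.585)/(0.30/0.70) = 1.66 and the risk ratio 0.415/0.30 = 1.38, so the absolute difference helps the reader.

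The cost of either is that size is approximate, about 5.0–5.1% for the chi-square at common rates of 30–36%, rather than guaranteed at or below 5%. The size of any gain from adjustment is an assumption, since the article gives nothing from which to estimate it.

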## Discussion

Current guidelines on treatment of STEMI recommend UFH as one of anticoagulant agents in patients undergoing PPCI, but the exact timing is not defined [1, 2]. Multiple observational studies and subgroup analyses have reported beneficial effects of pretreatment with UFH on the rate of spontaneous reperfusion of IRA [10–13]. To our knowledge, this is the first randomized trial investigating effects of pretreatment with UFH.

The duration of coronary thrombosis is likely to have a significant influence on effectiveness of UFH on the patency of IRA as indicated in one observational study [13]. With a longer duration of coronary thrombosis, the composition and organization of a thrombus are changing, making it less susceptible to endogenous fibrinolysis and also making UFH less effective. To show effectiveness of early UFH administration, we limited the patient population only to those with the duration of symptoms at less than 6 hours. We decided against any age limitation for our inclusion criteria to mimic the real patient population. However, we decided to exclude patients who remain unconscious after cardiac arrest and those in cardiogenic shock at the time of randomization. These patients represent a different subpopulation and would at this point only complicate the interpretation of results.

Side effects of early UFH administration are unlikely since it is an established practice and so far, we did not observe any higher rates of bleeding.

The trial is not blinded. Distribution of placebo or heparin to all prehospital units and education of all emergency physicians would be too complicated and costly. However, we tried to reduce chances of bias as much as possible. We decided for central computer-based randomization by consulting cardiologist/intensivist. An experienced interventional cardiologist who reviews and evaluates patient TIMI flow is not involved in patient care and will also be blinded to patient assignment. The culprit artery will be determined based on the ECG and angiographic features at the first coronary angiography. An acute culprit lesion was defined as abrupt occlusion or TIMI 2/3 flow with angiographic images suggestive of thrombus or ulcerated plaque [14].

Bleeding is assessed by the nurses in the intensive care unit and recorded in an established protocol for monitoring patients after coronary angiography.

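### Two pre-defined subgroups are cut on heparin time, which is the randomised contrast: one has no valid control comparison, the other compares patients with different ischaemic times

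*Protocol article*

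**What the plan says.** Under Assignment of interventions, the protocol article places randomisation before any heparin: "Patient randomization is performed directly after establishing diagnosis of STEMI and decision for PPCI has been made". The early arm then receives "Immediate application of UFH intravenously". The control arm receives "Standard treatment and application of intravenous UFH only after diagnostic coronary angiography at a recommended dose", and this is conditional on PPCI being performed. The primary endpoint (Outcome definitions) is TIMI flow on the diagnostic angiogram, so in controls it is read before any protocol heparin is given.

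The Data analysis section states the intention-to-treat principle for all data. It then lists five pre-defined subgroup variables: sex, age, culprit artery and two time variables. The first time variable has three levels: "time from onset of symptoms to heparin administration (<2 hours, 2–4 hours, >4 hours". The second is split once, at one hour, and is worded as "time from heparin administration to diagnostic angiography (<1 hour, >1 hour". The article names no substitute clock for controls. It neither restricts these two cuts to the early arm nor calls them descriptive.

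The Discussion gives the reason for interest in time: "The duration of coronary thrombosis is likely to have a significant influence on effectiveness of UFH on the patency of IRA".

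**The concern.** A subgroup variable for a randomised comparison should be fixed before treatment, or at least be measured in the same way in both arms. Heparin time meets neither condition. The allocation sets it, so stratum membership depends on the arm.

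At stake is the credibility of two planned subgroup results. One cannot be computed as a comparison of arms. The other can be computed, but it no longer compares like with like, and a reader would have no means of telling a weak effect in a stratum from a product of the definition.

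**Working it through.** **1. Heparin to angiography (no modelling needed).** For a patient treated per protocol:

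- Early arm: heparin is given at about randomisation and angiography follows. The interval is positive.
- Control with PPCI: angiography comes first, then heparin. The interval is negative.
- Control without PPCI: no protocol heparin. The interval does not exist.

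The stratum above one hour therefore has 0 per-protocol controls, and any control found there is a protocol deviation. The stratum below one hour also has none, unless negative values are counted as less than one hour, in which case all heparin-treated controls fall in it. Neither reading gives a valid odds ratio by stratum.

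**2. Onset to heparin.** Let T be onset to randomisation and D the delay from randomisation to control heparin (transfer plus angiogram).

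- Early arm: onset to heparin ≈ T.
- Control with PPCI: onset to heparin ≈ T + D.
- Control without PPCI: missing. This is settled at the same angiogram on which the endpoint is read, so the loss may be related to the outcome.

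A stratum from a to b hours holds early-arm patients with a < T < b and controls with a − D < T < b − D.

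**3. Size with no treatment effect.** The article gives no distribution of T or D and no patency slope. Assumptions: T uniform on 0.25 to 6 h, D = 1 h for all, 300 per arm, TIMI 2/3 about 30% at T = 3 h, log-odds of patency falling 0.2 per hour, all controls receiving heparin. Expected count = 300 × (width of the T range) / 5.75. Approximate stratum OR = exp(−0.2 × difference in mean T).

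| Stratum | T range, early | T range, control | Count, early | Count, control | Difference in mean T | OR by formula | OR simulated |
|---|---|---|---|---|---|---|---|
| <2 h | 0.25–2 | 0.25–1 | 91 | 39 | 1.125 − 0.625 = 0.5 h | 0.90 | 0.92 |
| 2–4 h | 2–4 | 1–3 | 104 | 104 | 3 − 2 = 1.0 h | 0.82 | 0.82 |
| >4 h | 4–6 | 3–6 | 104 | 157 | 5 − 4.5 = 0.5 h | 0.90 | 0.90 |

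The overall OR is 1.00, yet every stratum lies below 1. Other delays, simulated: 0.5 h gives 0.96/0.90/0.95. At 1.5 h the ORs are 0.86/0.75/0.86, with about 91 against 13 patients in the first stratum. At 2 h that stratum has no controls and the other two give 0.68 and 0.81.

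**4. Size under the design effect.** The sample-size section uses TIMI 0/1 rates of 58.5% and 70%. The unpooled formula gives (1.960 + 0.842)² × (0.585 × 0.415 + 0.70 × 0.30) / 0.115² = 268.7, so 269 per arm and 538 in total, as the article states. The odds ratio for TIMI 2/3 is (0.415/0.585) / (0.30/0.70) = 1.655.

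Simulations held this OR constant over time. They assumed lognormal T (median 1.5 to 2 h, cut at 6 h), gamma delay (mean 0.75 to 1.5 h) and a fall in log-odds of 0.15 to 0.30 per hour of ischaemia up to angiography. With a log-scale SD of 0.6 and gamma shape 4, cutting on onset to heparin gives:

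- median 1.5 h, delay 1 h, slope 0.15: 1.51/1.44/1.46
- median 1.5 h, delay 1 h, slope 0.30: 1.38/1.28/1.30
- median 2 h, delay 1.5 h, slope 0.30: 1.16/1.14/1.20

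Over the scenarios tried, the stratum ORs ran from about 1.1 to 1.56. Cutting the same data on onset to randomisation returned about 1.6 to 1.7.

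**5. Against sampling error.** With the counts in step 3, the SE of the log OR in the first stratum is √[1/(92 × 0.385 × 0.615) + 1/(39 × 0.406 × 0.594)] = 0.39. It is about 0.30 in the other two. The shifts are |ln 0.92| = 0.08, |ln 0.82| = 0.20 and |ln 0.90| = 0.11, that is about 0.2, 0.7 and 0.4 of a standard error.

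**The case against.** **These are supportive analyses.** They are two of five subgroup variables, with no alpha, power or decision rule attached. The primary, secondary and safety comparisons, the sample size and the other subgroups do not depend on them. This stands and limits the severity.

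**The cuts may be meant within the early arm only.** On that reading, having no controls above one hour is a matter of unstated scope, which an unseen analysis plan could settle. This is possible for heparin to angiography. But both variables are listed beside sex, age and culprit artery, which are between-arm subgroups, and nothing in the article separates them. The variables and cut-points are fixed in the text, not left open. A within-arm analysis would also not be a randomised comparison.

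**The size rests on assumptions.** Correct. The share of controls randomised within two hours who leave the first stratum ranged from 37% to 91% with the assumed spread and delay. At the planned size the bias is generally no more than about one standard error.

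**Stronger readings to avoid.** A reader might infer that the subgroups would show a false time gradient. The documents do not support that: the shape across strata depends on the assumed delays and on which clock drives patency, and in the scenarios above the pattern is mainly attenuation. A reader might also infer that these subgroups test the trial's stated hypothesis. The Conclusions state that hypothesis as early against late heparin. Time dependence appears as an observational result and as the ground for the six-hour limit.

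**Conclusion.** The point holds for both variables, with different force. For heparin to angiography it follows from the arm definitions alone: no valid between-arm comparison exists as defined. For onset to heparin, the lack of comparability also follows from the arm definitions. Its effect on the result further requires that patency falls with ischaemic time, which the Discussion's reasoning on thrombus ageing suggests. The bias then runs against early heparin within strata. It would tend to hide a real effect, not create one. The illustrative size is a true OR of 1.66 read as roughly 1.1 to 1.55, under assumed delays and slopes that the article does not supply.

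Nothing here weakens the primary intention-to-treat comparison, and it would be wrong to read the point that way. It should be fixed before analysis, but it does not threaten the trial's main result.

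**What to change.** - **Onset to heparin:** replace with time from symptom onset to randomisation, keeping the cuts <2, 2–4 and >4 h. It is settled before treatment and means the same in both arms.
- **Heparin to angiography:** replace with expected transfer time, or distance of the referring site, as known at randomisation. Time from randomisation to angiography is a second choice, because it is measured after randomisation in an open-label trial.
- **Analysis:** assess each by a treatment-by-time interaction, preferably with time continuous and the strata for display.
- **Actual heparin-to-angiography time:** keep it only as a description within the early arm, labelled as non-randomised.

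The cost is mainly wording in the protocol and analysis plan. Two downsides remain. The subgroups will no longer describe actual heparin timing. Onset time and expected transfer time must also be available for both arms; the case report form is not shown, so this has to be checked before the change is called free.
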